#### Criteria for discontinuing or modifying allocated interventions {11b}

If a patient experiences intolerable side effects when taking 0.2 mg naldemedine or placebo daily, a single downward dose titration to one tablet every other day is allowed, with this dose being the final dosage for the remainder of the study. Typical side effects associated with naldemedine are diarrhoea, abdominal pain, and other mild gastrointestinal symptoms. These treatment-related symptoms are not associated with a higher discontinuation rate than placebo [16].

A participant should be withdrawn from trial, if at any time:It is the wish of the participant for any reasonThe investigator judges it necessary due to medical reasonsThe investigator judges severe non-compliance to protocolThey experience intolerable side effects despite tapering the dose of naldemedine to 0.2 mg (or matching placebo) every other day

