#### Secondary outcomes

Difference between treatment groups in disease severity assessed by the Atlanta CriteriaThe difference between treatment groups in frequency and severity of pain attacks (without fulfilling acute pancreatitis criteria), assessed by questionnaires and monthly interviews after the 12-month periodDifference in patient’s global impression of change between treatment groups assessed by a questionnaire at 12 months follow-upChanges in quality of life between treatment groups from baseline to 12 months follow-up assessed by a questionnaireChanges in gastrointestinal symptoms and bowel function between treatment groups from baseline to 12 months follow-up assessed by questionnairesProportion of patients with new-onset diabetes according to the WHO criteria [18] and changes in endocrine pancreas function between treatment groups from baseline to 12 months follow-up assessed by haemoglobin A1c (HbA1c)Proportion of newly diagnosed exocrine pancreatic insufficiency defined by the use of pancreatic enzyme replacement therapy or changes in exocrine pancreas function between treatment groups from baseline to 12 months follow-up assessed by a faecal-elastase testDifference between treatment groups in health care resource utilization (measured in frequency and type of health services used, e.g. admission rate and duration) during the 12-months treatment periodDifference between treatment groups in adherence to treatment and frequency of adverse events during the 12-months treatment period assessed by study drug diary, return of unused medicine, and regular interviews

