#### Plans to promote participant retention and complete follow-up {18b}

All patients will be followed by monthly telephone interviews with the study personnel during the entire study period and visits in the outpatient clinic at baseline and 12 months. If a participant does not turn up for a scheduled visit, every effort will be made to contact the participant. In any circumstance, every effort will be made to document the participant’s health status. In case of discontinuation or withdrawal from the study before the planned 12 months period, the patient is subsequently invited to a premature “end of study”-visit, which includes an MRI scan, blood samples, and questionnaires to ensure data completeness.

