### Statistical methods

#### Statistical methods for primary and secondary outcomes {20a}

The Andersen-Gill model is applied for the statistical analyses of the primary endpoint. It is an extension of the Cox model and can be used for recurrent event analyses. This analysis enables efficient use of patient data since the same patient can contribute with multiple events in case of more than one recurring pancreatitis attack over the 12-month treatment period. The output of the analysis is a hazard ratio indicating whether naldemedine-treated patients have a lower hazard of recurring pancreatitis events compared to placebo. All analysis will be done with the intention to treat principle. Secondary endpoints, including questionnaires, biochemical parameters, and MRI assessment parameters, are analysed using regression models. Logistic regression models are used to compare dichotomous outcomes between treatment groups.

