#### Adverse event reporting and harms {22}

Any clinically significant abnormalities will be reported as an AE. The primary investigator is responsible for the assessment of clinical significance. Since the patients included in the study suffer from a severe medical condition, they are expected to develop specific symptoms and laboratory result deviations frequently associated with the disease during the study period. The symptoms and associated conditions have been presented to the regulatory authorities and pre-approved to be excluded from AE reporting.

AE's and adverse reactions will be registered until 55 h after the study medication is discontinued. This timeframe corresponds to five times the half-life of naldemedine, which is 11 h [31]. All expected or unexpected AEs and adverse reactions are registered in the CRF. They are reported in a final report which will be recorded into EudraCT along with the results at the trial's termination. Information about AEs will be collected from the first administration of any investigational product until the end of the study. The Research Ethics Committee and Medicines Agencies will annually be presented with a list of all serious adverse reactions and suspected unexpected serious adverse reactions that have occurred during the trial, along with an evaluation of patient safety until the trial has concluded. All fatal or life-threatening suspected unexpected serious adverse reactions are reported to the Health and Medicines Authorities and The Research Ethics Committees as soon as possible and no later than seven days after the sponsor has been notified of suspected unexpected serious adverse reactions.

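### Adverse events are compared over 12 months under a blanket intention-to-treat rule, but with two stated recording windows; raw counts would be understated in whichever arm stops treatment more

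*Protocol article*

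**What the plan says.** All references are to the protocol article.

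- **Secondary outcomes.** The arms are compared on adherence and on "frequency of adverse events during the 12-months treatment period". The metric (events, patients with an event, or a rate) is not defined.
- **Statistical methods for primary and secondary outcomes {20a}.** "All analysis will be done with the intention to treat principle". No exception is made for safety.
- **Adverse event reporting and harms {22}, first window.** "AE's and adverse reactions will be registered until 55 h after the study medication is discontinued". The reason given is pharmacokinetic: "This timeframe corresponds to five times the half-life of naldemedine, which is 11 h".
- **The same section, second window.** "Information about AEs will be collected from the first administration of any investigational product until the end of the study".
- **Criteria for discontinuing or modifying allocated interventions {11b}.** Intolerable side effects that persist after the permitted dose reduction lead to withdrawal from the trial. On expected stopping, the section says of the typical side effects: "These treatment-related symptoms are not associated with a higher discontinuation rate than placebo".
- **Plans to promote participant retention and complete follow-up {18b}.** After early discontinuation or withdrawal, "the patient is subsequently invited to a premature “end of study”-visit".
- **Provisions for post-trial care {30}.** Patients who discontinue return to routine visits. Events still unresolved at the end of the study are followed until they resolve or are judged stable.

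**The concern.** The outcome is labelled as a 12-month comparison of all randomised patients. Under the first recording window, a patient who stops in month 2 contributes about two months of events and still counts as a full patient in the denominator. One route to stopping is poor tolerability, so harm can shorten the period in which harm is recorded.

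The second window does not clearly repair this. If the end of the study means month 12 for every patient, section {22} contradicts itself for anyone who stops early. If it means the premature final visit of section {18b}, both windows close early and observation is short under either.

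The Discussion says that compliance and adverse events are collected to document the feasibility of long-term naldemedine treatment. A diluted adverse event contrast would bear directly on that conclusion.

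**Working it through.** **The plan's own figure.** 5 × 11 h = 55 h, as stated. In months, 55 h ÷ 730.5 h = 0.075.

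**Inputs not in the documents.** No adverse event rate, discontinuation share or time of stopping is given. All such values below are assumptions.

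**Step 1. Recorded ratio when the true rates are equal.** Let a share *p* stop at month 2, with recording to last dose plus 55 h.

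Observed months per randomised patient = (1 − *p*) × 12 + *p* × 2.075

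| *p* | Observed months | Ratio to placebo at 5% |
|---|---|---|
| 5% | 11.40 + 0.10 = 11.50 | 1.00 |
| 10% | 10.80 + 0.21 = 11.01 | 0.96 |
| 20% | 9.60 + 0.42 = 10.02 | 0.87 |
| 30% | 8.40 + 0.62 = 9.02 | 0.78 |

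At 20% against 5%, a true excess of 1 ÷ 0.87 = 1.15 would be recorded as no difference. With the same stopping share and timing in both arms, the ratio is 1.00.

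**Step 2. Recorded ratio when there is a true excess.** Let *d* be the share stopping, *t* the fraction of the year at which they stop, and *r* the true on-drug rate ratio.

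- Observed fraction of the year: *f* = 1 − *d*(1 − *t*) + *d* × 55/8766
- Recorded ratio: *r* × *f*(naldemedine) ÷ *f*(placebo)
- Ratio if everyone were recorded to month 12, with off-drug events at the placebo rate: *r* × *f*(naldemedine) + 1 − *f*(naldemedine)

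Placebo is fixed at *d* = 10%, *t* = 0.25, so *f* = 0.926. Take *r* = 1.5:

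| Naldemedine *d*, *t* | *f* | Recorded ratio | Full 12-month ratio | *r* at which the recorded ratio is 1 |
|---|---|---|---|---|
| 10%, 0.25 | 0.926 | 1.50 | 1.46 | 1.00 |
| 20%, 0.25 | 0.851 | 1.38 | 1.43 | 1.09 |
| 30%, 0.25 | 0.777 | 1.26 | 1.39 | 1.19 |
| 40%, 0.10 | 0.643 | 1.04 | 1.32 | 1.44 |

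With unequal stopping, the raw count recovers neither the on-drug ratio (1.5) nor the full 12-month ratio. A sizeable excess shrinks but is not reversed in these cases.

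**Step 3. Would a crude rate per patient-month be enough?** Suppose both arms have 1 event per patient in months 0–2 and 0.05 per month afterwards, so a full year gives 1 + 10 × 0.05 = 1.5. Let 20% (naldemedine) and 5% (placebo) stop at month 2, ignoring the 55 h.

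- Counts: 0.80 × 1.5 + 0.20 × 1 = 1.400, and 0.95 × 1.5 + 0.05 × 1 = 1.475. Ratio 0.95.
- Months: 0.80 × 12 + 0.20 × 2 = 10.0, and 0.95 × 12 + 0.05 × 2 = 11.5.
- Rates: 0.140 and 0.128. Ratio 1.09.

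The truth is 1.00. When events cluster early, the crude rate errs in the other direction and by more. A method that compares the arms at the same time since first dose returns 1.00 here, because the rates are equal at every time point.

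**The case against.** The strongest case against the point has five parts.

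1. **Equal stopping is expected.** Section {11b} says the typical side effects do not raise discontinuation above placebo, and with equal stopping there is no distortion. This stands as the article's expectation. It is a cited external result, however. The Background says this drug class has never been investigated for this indication, and the trial makes adherence by arm an outcome. The adverse event comparison should not depend on that expectation.
2. **The events that matter most are recorded.** A side effect that causes stopping occurs on drug. If frequency means patients with at least one event, each such patient is already counted. This stands: the loss falls mainly on event counts and on later events.
3. **The analysis plan may settle the metric.** Safety sets and exposure adjustment are commonly left to it, and intention to treat does not itself forbid person-time. This stands, so the absence of those details is not the point. What the article does state is a rule covering all analyses and two recording windows. An analysis plan that used a treated set would depart from the first and would have to choose between the second.
4. **Five half-lives is a coherent on-treatment window.** Agreed. The difficulty arises only when it feeds a comparison labelled as 12-month intention to treat.
5. **Other provisions help.** Adherence is compared in the same outcome item, so unequal stopping would be visible, and unresolved events are followed up. Neither supplies new events that occur after recording has closed.

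**Conclusion.** The point holds in conditional form. The article pairs a 12-month, all-randomised comparison with two recording windows that differ for early stoppers unless their study ends at withdrawal. If stopping differs by arm, raw counts per randomised patient are understated in the arm that stops more. Under the assumed inputs, the recorded ratio is the true ratio multiplied by 0.96 to 0.78 in step 1. In step 2, a true 1.5 is recorded as 1.38 to 1.04. If stopping is equal, the effect is nil.

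Two stronger readings are tempting, and the documents support neither.

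- A reader might infer that naldemedine *will* appear to cause fewer adverse events. That needs more stopping on naldemedine, which the article does not expect, and a true on-drug ratio below about 1.1 to 1.4 in the step 2 scenarios.
- A reader might infer that reconciling the two windows cannot help. Recording every patient to month 12 would equalise observation time and remove this distortion. It persists if the windows are reconciled to 55 h, or if a patient's study ends at withdrawal.

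The wording is worth correcting because adverse events support a stated conclusion on feasibility, and the correction is cheap.

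**What to change.** 1. In section {22}, reconcile the two recording windows, and say what the end of the study means for a patient who stops early.
2. In section {20a}, exempt adverse events from the sentence that applies intention to treat to all analyses.
3. If the window ends at last dose plus 55 h, analyse adverse events in patients who took at least one dose, with follow-up censored at that point. Use a method that allows for time at risk and a changing rate: for example the mean cumulative number of events by arm, or the Andersen-Gill model already specified for the primary endpoint. Give a rate per patient-month only as a summary, for the reason in step 3.
4. Report time to discontinuation or dose reduction for an adverse event, by arm, beside that comparison. Censoring at drug stop is itself related to tolerability, so the two results need to be read together.

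The cost is wording in the protocol or analysis plan and a little more analysis. The drug diary and medication counts should supply the exposure dates. The on-treatment version describes harm while patients take the drug, not over the full 12 months after randomisation, and should be labelled so. If stopping proves equal, the raw comparison would not have been distorted and only the extra analysis has been spent.

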#### Explorative outcomes

Changes in pancreatic morphology (pancreas volume/size, fibrosis, fatty infiltration, and ductal pathology) between treatment groups from baseline to 12 months follow-up measured by MRIDifference in circulating markers of fibrosis and inflammation from baseline to 12 months follow-up

#### Participant timeline {13}

The participant timeline is shown in Table 1.

**Table 1 Tab1:**
[figure not shown]
Schedule for enrolment, interventions, and assessments including visits for patients

^**a**^Baseline variables: sex; age; the number of recurrences of acute pancreatitis before inclusion, presence of chronic pancreatitis and aetiology of pancreatitis; use of opioids, weak analgesics, and other medication; alcohol consumption and smoking status; Information regarding diabetes mellitus and use of pancreatic enzyme replacement therapy; Previous invasive treatment for pancreatitis; Comorbidities based on the Charlson Comorbidity Index [19]

^**b**^Verified recurrence(s) and severity of acute pancreatitis based on the Atlanta Criteria and pain attacks not fulfilling the Atlanta Criteria; Pain attack diary and the modified Brief Pain Inventory Short Form are filled in once for each attack

^**c**^Patient Global Impression of Change questionnaire and European Organization for Research and Treatment of Cancer Quality of Life questionnaire (EORTC QLQ-C30); Gastrointestinal Symptom Rating Scale and Bristol Stool Form Scale

^**d**^Study drug diary and adverse events diary

*Magnetic resonance imaging

#### Sample size {14}

The sample size calculation is based on the following assumptions:Included recurrent acute pancreatitis patients will have one pancreatitis attack at least once pr. yearNaldemedine is expected to reduce the pancreatitis attack rate by 50%Power is set to 90% at a 2-sided alpha level of 0.05

These assumptions analysed by the extended (recurrent) Cox model yield a required sample size of 120 patients observed for 12 months. We implement a planned interim analysis after 60 participants have been enrolled to allow re-estimation of sample size requirements and to examine adverse event rates.

#### Recruitment {15}

For patients with recurrent acute pancreatitis, recruitment material will be placed in waiting rooms at the outpatient clinics. Patients interested in participating in the study may contact study personnel for further information. Furthermore, to identify eligible patients with recurrent acute pancreatitis from the respective departments or outpatient clinics, medical history and previous treatment can be passed on from the treatment-responsible physician from medical records to study personnel. Potentially eligible patients from the outpatient clinic may be contacted by study personnel, but only if the treatment-responsible physician has granted permission. Patients can be assessed for inclusion 4 weeks after discharge from a pancreatitis attack if they are clinically stable at the time of inclusion. The expectation is to enrol five patients per week at the five inclusion sites.

### Assignment of interventions: allocation

#### Sequence generation {16a}

Randomization is performed in blocks (block-randomization) using approved statistical software. Since opioid consumption is assumed to be an important prognostic variable, patients will be stratified before randomization creating two strata based on opioid treatment. Naldemedine and matching placebos will be requisitioned and delivered by the Hospital Pharmacy at Aalborg University Hospital. All medication will be labelled with the randomization number corresponding to the allocation and clearly state that it is only intended for use in a clinical trial.

#### Concealment mechanism {16b}

The Hospital Pharmacy will create a randomization list at Aalborg University Hospital based on the sequence described above. The list is sequentially numbered, where newly included patients are assigned the lowest available number consecutively.

#### Implementation {16c}

After inclusion, the Hospital Pharmacy will assign a specific randomization number to the individual patient from a predefined randomization list. This randomization number will be returned to study personnel, blinded to the allocation alongside the participants. None of the collected data are expected to unblind the randomization.

### Assignment of interventions: blinding

#### Who will be blinded {17a}

In this double-blind study, labelling and blinding is performed by Wasdell Europe Limited, according to Annex 13 of the Good Manufacturing Practice guidelines of the European Commission, ICH, GCP guidelines. Research pharmacists perform subsequent handling and distribution of the investigational medicine at the Hospital Pharmacy at Aalborg University Hospital. This blinding mechanism ensures that personnel and participants directly involved in the project are prevented from obtaining information that might bias the results.

#### Procedure for unblinding if needed {17b}

If a participant needs urgent medical care that requires knowledge of the given treatment randomization, the treatment allocation for each participant is available at the study centres in sealed envelopes (provided by the Hospital Pharmacy at Aalborg University Hospital). They are stored in a secure area accessible to personnel involved in the study authorized by the investigator to open the code for a single subject. This procedure allows unblinding of individual subjects without revealing the codes of the entire study. Thus, the study personnel can determine which treatment a subject was given by opening the sealed envelope with the corresponding randomization number.

## Data collection and management

### Plans for assessment and collection of outcomes {18a}

#### Clinical outcome and health resource utilization

The clinical outcomes will be documented through questionnaires and a pain attack diary, filled in before, during, and after treatment. Participants will be asked to fill in the pain attack diary, and the modified Brief Pain Inventory Short Form for each pancreatitis attack during the study period. Hospital admissions and whether patients fulfilled the Atlanta criteria for acute pancreatitis during admission will subsequently be documented using the medical files along with the severity of the attack. To assess the effects of the treatment on quality of life, patients will also be asked to fill in the following: (i) the European Organization for Research and Treatment of Cancer Quality of Life Questionnaire (EORTC QLQ-C30) and (ii) the Patient Global Impression of Change Questionnaire. For a detailed description of these questionnaires, see the section below. The patients’ medical files at 12 months follow-up are used to document health resource utilization, readmission rate, and total length of hospital stays during the recovery phase of pancreatitis.

#### Pain attack diary

The number and severity of pain attacks are registered by the patient in a paper diary, documenting the duration of each pain attack and the need for medication or hospital admission. Participants will also be asked to phone study personnel in connection to each attack.

#### The modified Brief Pain Inventory Short Form

The modified Brief Pain Inventory Short Form is used to subjectively document patients’ pain if pain attacks are experienced during the treatment period. The questionnaire consists of 14 items based on a visual analogue scale from 0 to 10 documenting current pain, pain within the previous 24 h, and impact on various daily functions [20].

#### Patient Global Impression of Change

Patient Global Impression of Change is a seven-point rating scale for self-reporting a patient’s overall experienced treatment efficacy on their symptoms [21], which is filled out at the end of the study visit after 12 months.

#### The European Organization for Research and Treatment of Cancer Quality of Life

The EORTC QLQ-C30 Questionnaire is used to document life quality, physical function, and several other health-related parameters [22] and will be filled in by participants at baseline and 12 months follow-up. The questionnaire has been validated for assessing the quality of life in patients with chronic pancreatitis and is composed of single-item measures and multi-item scales by scores ranging from 0 to 100 after linear transformation of the raw score [23]. A high score on the functional scale represents a high level of functioning, as does a high score for global health status, while a high score for the symptom items represents a high level of symptomatology.

